## Methods

### Ethics Approval

Eligible participants should provide written informed consent after reviewing consent documents with medical staff. To protect participant privacy and confidentiality, questionnaire surveys for the evaluation of cognitive function should be completed by research staff in a secure office in the inpatient ward. Only trained research staff have access to the key that can match participant data to the participant’s name. This trial has been approved by the ethics committee of Nanjing First Hospital (approval KY20230310-05-KS-0I), and the collaborator of Jiangsu Health Vocational College provides ongoing oversight. This study was registered in ClinicalTrials.gov (NCT05876988) on April 13, 2023, before the first participant was recruited.

### Study Design

We present a protocol for a 2-arm, prospective, randomized, assessor-blinded trial to examine the efficacy and safety of EA for chemobrain among older patients with cancer who are undergoing chemotherapy or those are going to just begin chemotherapy. This study refers to a double-blinded trial in which neither the investigator nor the participant knows the group to which the participant belongs (experimental group or control group), and the analyst usually does not know which group the data being analyzed belong to. This study is designed to eliminate subjective biases and personal preferences that may arise in the consciousness of investigators and participants. Those who report clinically significant cognitive impairment are being recruited and enrolled to participate in a trial on the effects of a novel EA intervention to address negative mood symptoms and reduce chemotherapy-induced adverse reactions. Participants are recruited via community organizations, social media, and internet outlets (eg, hospital classified ads, WeChat). Interested older patients with cancer complete a screener assessment by the medical staff of the Oncology department or a Chinese medicine doctor, and they report the levels of cognitive dysfunction they are experiencing through the Overall Anxiety Severity and Impairment Scale [20] and the Overall Depression Severity and Impairment Scale [21]. Those eligible at the screener complete an enrollment for full eligibility and receive instructions on how to accept EA therapy to complete the baseline assessment. Additionally, eligible participants will be randomly assigned to either an experimental group or a control group at 1:1 ratio. Participants then engage with the assigned intervention for 8 weeks following randomization. Participants complete follow-up assessments at baseline, 2, 4, 6, and 8 weeks after randomization, which include the MoCA, Digit Span Test, QoL, and multiple functional assessments. Additionally, participants are prompted to complete ecological momentary assessments [22] twice weekly throughout the 2-month postrandomization period. The study flow diagram is shown in Figure 1.

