**Methods:**

This study involves a 2-arm, prospective, randomized, assessor-blinded clinical trial in older patients with cancer experiencing chemobrain-related stress and treated with Chinese acupuncture from September 30, 2023, to December 31, 2025. We will enroll 168 older patients with cancer with clinically confirmed chemobrain. These participants will be recruited through screening by oncologists for Chinese acupuncture therapy and evaluation. Electroacupuncture will be performed by a registered practitioner of Chinese medicine. The electroacupuncture intervention will take about 30 minutes every session (2 sessions per week over 8 weeks). For the experimental group, the acupuncture points are mainly on the head, limbs, and abdomen, with a total of 6 pairs of electrically charged needles on the head, while for the control group, the acupuncture points are mainly on the head and limbs, with only 1 pair of electrically charged needles on the head.

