### Participants and Recruitment

This 2-arm, prospective, randomized, assessor-blinded trial will be conducted from September 2023 to December 2025 in the Department of Oncology/Chinese Medicine, Nanjing First Hospital, China. Potentially eligible participants would be screened and recruited through clinical oncologists/Chinese medicine acupuncturists’ referral from local hospitals and advertisements. Enrollment to this study began in September 2023 and, as of writing this paper, is in the recruitment phase. Enrollment, randomization, intervention delivery, and assessments are completed by trained research staff. Both study conditions receive the same set of questionnaires at each assessment (see Figure 2) or the full list and timeline of study measures. These questionnaires assess chemobrain symptoms, functional impairment, general and chemotherapy-specific affect constructs, and sociocultural factors. Interested individuals complete an initial screener to assess age, racial/ethnic identity, clinical confirmation of chemobrain, state of residence, and willingness to complete study assessments. During the enrollment, volunteer participants will be asked to sign written informed consent forms and are informed of the purpose, goals, and procedures of the study. All participants will give voluntary, written, and informed consent before entering the trial.

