### Questionnaires/Instruments

#### MoCA Self-Reported Questionnaire

The MoCA self-reported questionnaire is the main method used for assessing cognitive function. To objectively measure the cognitive impairment patterns of the participants, MoCA, a sensitive, time-sparing tool with high diagnostic validity, will be used to measure the degree of chemobrain. We evaluate the utility of MoCA as a chemobrain screening test for older patients with cancer who are undergoing or about to receive chemotherapy. Participants will be instructed to self-report their cognitive functions through MoCA for 5 consecutive timepoints from baseline to the end of the 8-week treatment. Statistical software will be used to analyze participants’ cognitive function information recorded in case report forms.

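### Screening grades cognitive dysfunction with an anxiety scale and a depression scale, no cognitive measure is named for entry, and the entry population is described in conflicting ways

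*Protocol article*

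**What the plan says.** On the screening instrument, Study Design says of interested patients that "they report the levels of cognitive dysfunction they are experiencing through the Overall Anxiety Severity and Impairment Scale" and "the Overall Depression Severity and Impairment Scale". It then makes the screener a gate: "Those eligible at the screener complete an enrollment for full eligibility". No cutoff is stated for either scale.

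On who is enrolled, the protocol article gives several descriptions:

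- Abstract, Methods: "We will enroll 168 older patients with cancer with clinically confirmed chemobrain".
- Study Design: "Those who report clinically significant cognitive impairment are being recruited and enrolled".
- Participants and Recruitment: "Interested individuals complete an initial screener to assess age, racial/ethnic identity, clinical confirmation of chemobrain, state of residence, and willingness to complete study assessments". How the confirmation is made is not stated, and neither mood scale appears in this list.
- Inclusion and Exclusion Criteria: a malignancy, age 60 or older, and chemotherapy in progress or about to start. There is no cognitive, anxiety or depression criterion.
- Sample Size Estimation: chemobrain incidence of 30% after chemotherapy, to be reduced by acupuncture.
- Statistical Analyses: a Kaplan-Meier comparison of cognitive deficits accumulating over 8 weeks.

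On measuring cognition, Study Procedures and Assessments assign cognitive performance to MoCA and FACT-Cog, both collected at T0. The MoCA section adds: "We evaluate the utility of MoCA as a chemobrain screening test for older patients with cancer". Statistical Analyses defines cognitive impairment by a 1.5 SD rule on MoCA and QLQ-C30. None of these is tied to entry.

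**The concern.** A scale of anxiety or depression severity does not grade cognition. A site that followed Study Design literally could count a distressed patient with intact cognition as having cognitive dysfunction, and could record little dysfunction in a forgetful patient who is not distressed.

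Two things are at stake. The first is whether the enrolled patients are those to whom the result will be applied. The second is whether the outcome fits the population. A trial of treatment needs patients with impairment that can improve, whereas a trial of prevention needs patients who are not yet impaired. The protocol supports both readings and gives no cognitive measure at entry by which to tell the two kinds of patient apart.

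**Working it through.** The protocol article states no figure for this point that could be reproduced, so the check is mainly a comparison of the text.

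**1. Is the mislabelling a single slip?** No. Specific Aims and Hypotheses runs the same anxiety scale together with MoCA in one hypothesis and predicts reductions in both. Study Design also describes the intervention as directed at negative mood. The other sections on cognition use MoCA, FACT-Cog or QLQ-C30, and none of them uses the mood scales for that purpose.

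**2. Does another section supply a cognitive measure for entry?** Participants and Recruitment lists "clinical confirmation of chemobrain" in the screener but gives no method. The formal criteria contain no cognitive item. The MoCA section calls MoCA a screening test but gives it no role in eligibility. The mood scales are therefore the only instruments that the text names for grading cognitive dysfunction at screening. The flow diagram and schedule figures are not shown, so this holds for the text only.

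**3. Can the descriptions of the population all be true?** Not as they stand. The criteria admit patients about to start chemotherapy and exclude those treated within the last 2 years. In a patient who has not yet started, confirmed chemobrain could come only from chemotherapy more than 2 years ago. Most such patients fit an at-risk population, not one with all 168 already confirmed.

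**4. What does this do to the incidence analysis?** Let f be the proportion already impaired at T0, and assume that entry status and the analysis definition agree. With 84 per group:

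- At risk of a new deficit, per group: 84 × (1 − f).
- Expected control-group cases at the protocol's 30%: 0.30 × 84 × (1 − f) = 25.2 × (1 − f), before dropout.

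If nobody is impaired at T0 (f = 0), 84 per group are at risk and about 25 control cases are expected. If everyone has confirmed chemobrain (f = 1), nobody is at risk and no new cases can occur. The document does not give f. These are the two ends of the range and not estimates. They also treat the 30% as applying within the 8 weeks, which the protocol does not say.

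**5. How much would selection on mood shift the population?** This cannot be computed. It needs a cutoff on each scale and the correlation between mood and cognitive scores in these patients, and the document gives neither.

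**The case against.** The strongest defence is that the mood scales may not select anyone. Study Design sets no threshold and never says that a high score admits a patient. The formal criteria ignore both scales. The Abstract and Participants and Recruitment refer to clinical confirmation of chemobrain, and screening is done by clinical staff. This stands, and it limits the finding. A reader might infer that the trial enrols distressed patients in place of patients with chemobrain. The documents do not show that; it is a risk if sites use the scales to select.

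A second objection also stands. Requiring an impaired MoCA for entry would conflict with the prevention aim in the Conclusions of the Abstract and in Assessments, with the 30% incidence assumption, and with the cumulative-incidence analysis. Selecting on a low T0 MoCA and then analysing change from T0 would also bring regression to the mean into the primary outcome within each arm. MoCA should therefore measure cognitive level at entry, and whether it also selects depends on which population is intended.

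A reader might further infer that spontaneous recovery of mood would bias the result. Regression to the mean would be expected in both arms and, on average, cancels in the randomised comparison. Nor is the lack of an exclusion for other causes of cognitive impairment a finding, since a condensed article may leave that to the full protocol.

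The defence does not remove the wrong statement about what the scales measure, or the conflict between the descriptions of the population. Both are in the text as written.

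**Conclusion.** The point holds in a limited form. Study Design assigns the grading of cognitive dysfunction at a gating screener to two scales that by name measure mood, and the text names no cognitive instrument for entry. The protocol also describes at least three populations that cannot all be the one enrolled: all confirmed, self-reported impaired, or unselected on cognition and at risk.

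The effect of the mood scales on who is enrolled is possible, but it is unquantified and not demonstrated. The effect of the population conflict can only be bounded. Depending on how many patients are already impaired at T0, the number per group at risk of a new deficit lies anywhere from 0 to 84. That range rests on the assumption that impairment at entry and impairment in the analysis mean the same thing.

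**What to change.** 1. In Study Design, replace the two mood scales with MoCA and FACT-Cog as the measure of cognitive level at entry. Keep the mood scales only as baseline descriptors or covariates; Statistical Analyses already plans to adjust for depression.
2. Reconcile the Abstract, Study Design, Participants and Recruitment, the eligibility criteria, Sample Size Estimation and Statistical Analyses on whether the trial enrols impaired patients (treatment), at-risk patients (prevention) or both.
3. If both, report results by baseline cognitive status and restrict the incidence analysis to patients unimpaired at T0.

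The cost is a short amendment. No new instrument or visit is needed, because both cognitive measures are already scheduled at T0 and baseline assessment already comes before randomisation. The added step is that T0 cognitive testing must be reviewed before the allocation envelope is opened. Restricting the incidence analysis reduces its numbers by the share impaired at T0, so its precision should be checked again once that share is known. Results reports 11 of 168 patients recruited by October 21, 2023. They can be kept and classified from their T0 assessments.

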**Figure 1 figure1:**
[figure not shown]
Participant flow diagram in the clinical trial.

### Specific Aims and Hypotheses

Chinese acupuncture is an emerging therapeutic option for chemotherapy-induced cognitive impairment in older patients with cancer, despite limited supporting evidence [23]. This study has 2 specific aims.

First, to evaluate the clinical therapeutic response of EA intervention for the treatment of chemobrain in older patients with cancer, a randomized controlled trial is designed to study the effects of EA on chemobrain at baseline, 2, 4, 6, and 8 weeks follow-up. We hypothesize that those assigned to EA will show greater reductions from baseline to follow-ups in MoCA Overall Anxiety Severity and Impairment Scale and Digit Span Test scores and greater reductions in cognitive impairment in daily responsibilities relative to the control group. We also hypothesize that the effectiveness of EA on QoL and multiple functional assessments will be similar across experimental or control groups.Second, our aim is to elucidate the modern biomedical mechanism of EA in the treatment of chemobrain in older patients with cancer. In testing the putative mechanisms of action, we hypothesize that the intervention effects on study outcomes will be mediated by reductions in chemotherapy-induced working memory impairment and the incidence of certain digestive, neurological, and distress-related symptoms.

### Participants and Recruitment

This 2-arm, prospective, randomized, assessor-blinded trial will be conducted from September 2023 to December 2025 in the Department of Oncology/Chinese Medicine, Nanjing First Hospital, China. Potentially eligible participants would be screened and recruited through clinical oncologists/Chinese medicine acupuncturists’ referral from local hospitals and advertisements. Enrollment to this study began in September 2023 and, as of writing this paper, is in the recruitment phase. Enrollment, randomization, intervention delivery, and assessments are completed by trained research staff. Both study conditions receive the same set of questionnaires at each assessment (see Figure 2) or the full list and timeline of study measures. These questionnaires assess chemobrain symptoms, functional impairment, general and chemotherapy-specific affect constructs, and sociocultural factors. Interested individuals complete an initial screener to assess age, racial/ethnic identity, clinical confirmation of chemobrain, state of residence, and willingness to complete study assessments. During the enrollment, volunteer participants will be asked to sign written informed consent forms and are informed of the purpose, goals, and procedures of the study. All participants will give voluntary, written, and informed consent before entering the trial.

**Figure 2 figure2:**
[figure not shown]
Schedule of enrollment, interventions, and assessments. T0: baseline; T1-T3: midpoint of main treatment once every 2 weeks; T4: end of the 8-week main treatment.

### Inclusion and Exclusion Criteria

The participants in this study are 168 older patients with cancer who are further assessed for eligibility and meet the following eligibility criteria: (1) have clinically pathological diagnosis of malignant tumor, (2) aged 60 years or older, and (3) are currently undergoing or just about to commence a comprehensive treatment of chemotherapy. The exclusion criteria are as follows: (1) undergone chemotherapy within the last 2 years; (2) metal device or pacemaker planted in the body, developed epilepsy, and experienced instability; (3) participated in a drug trial within the last 6 months; (4) alcohol or drug abuse history in the past year; and (5) those who are afraid of acupuncture.

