**Results:**

Eligible participants will be randomized to the control group or the experimental group in 1:1 ratio. The primary outcome of this intervention will be the scores of the Montreal Cognitive Assessment. The secondary outcomes, that is, attentional function and working memory will be determined by the Digit Span Test scores. The quality of life of the patients and multiple functional assessments will also be evaluated. These outcomes will be measured at 2, 4, 6, and 8 weeks after the randomization.

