**Conclusions:**

This efficacy trial will explore whether Chinese electroacupuncture can prevent chemobrain, alleviate the related symptoms, and improve the quality of life of older patients with cancer who are undergoing or are just going to begin chemotherapy. The safety of this electroacupuncture intervention for such patients will also be evaluated. Data from this study will be used to promote electroacupuncture application in patients undergoing chemotherapy and support the design of further real-world studies.

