### Randomization and Allocation Concealment

Older patients with tumors will be screened for eligibility, and enrollment and baseline assessments should be completed thereafter. A random code of simple, complete, and nonsequential numbers could be produced in advance from a computer-generated block randomization with random block sizes. Participants will be randomly assigned to experimental or control groups in a 1:1 ratio. Random information will be sealed in sequentially numbered opaque envelopes.

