### Assessments

In this study, therapeutic efficiency will be assessed in terms of the following aspects: cognitive performance, fatigue, QoL, and chemotherapy-induced side effects. The primary outcome of this study is to verify whether EA is therapeutically useful for preventing chemobrain and alleviating the related symptoms and the safety of intervention. Cognitive performance will be assessed using MoCA + FACT-Cog. The secondary outcomes are as follows: QoL will be measured using EORTC QLQ-C30, fatigue will be assessed using the FACIT-Fatigue scale, and the manifestation of chemotherapy-induced side effects will be assessed using the Chemotherapy Symptom Rating Scale FAACT + FACT-BRM. All assessment scales will be evaluated by previously trained researchers at the following timepoints (see Figure 2): baseline (T0), midpoint of main treatment (T1-T3) once every 2 weeks, and end of the 8-week main treatment (T4) (a total of 5 timepoints). We will also keep a record of all the shedding cases. This study is a multidisciplinary clinical trial (across oncology and Chinese medicine disciplines) on the role of Chinese acupuncture as therapy for chemotherapy-induced cognitive impairment in older patients with cancer. If successful, findings from this study might have beneﬁts in reducing chemotherapy-induced working memory impairment. Data from this study may be used to support an implementation and dissemination trial of Chinese EA in real-world behavioral health and social service settings.

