### Statistical Analyses

Cognitive impairment is defined as those with SD>1.5 in the mean scores of MoCA and the QLQ-C30 at baseline for all participants at different timepoints. A time-series test in the Kaplan-Meier survival analysis will be used to compare the incidence of cognitive deficits accumulated after 8 weeks of acupuncture intervention between the 2 groups. Linear mixed-effects modeling will be used to compare participants’ cognitive impairment, fatigue, and depression at baseline, during, and after acupuncture intervention, where only those who have completed at least one assessment at baseline and during treatment will be compared. This model will use time and group as categorical fixed factors and random intercepts and use random intercepts in conjunction with a measurement covariance matrix. Participants’ age, chemotherapeutic drug dosage, fatigue at baseline, depression, and additional treatments will be considered as covariates in the statistical analyses. A 2-sided *t* test will be used to compare the covariates at each timepoint between the 2 groups. The chi-square test will be used for qualitative information and the *t* test will be used for continuous information at baseline. Statistical significance will be considered at *P*<.05. The study data used will be statistically analyzed using SPSS software (IBM Corp) under the supervision of a statistician. To ensure the privacy of the patients, all relevant study data and personal data will be kept in a locked file cabinet. Electronic data will be stored on an encrypted computer and will not be stored on any external storage device. Each participant will be assigned his or her own ID in the study record, which will be used in lieu of his or her name and personal identifying information. Clinical data from the study will be kept in a separate file from the participant’s personal data. The principal investigator will be responsible for all the clinical trial data. During and after the clinical trial, the principal investigator, researchers, and the ethical review committee have the right to view the study data. Participants will have the right to access their personal data and the results of the study. All study data will be stored for a minimum of 3 years after the completion of the trial, after which they will be destroyed in accordance with the rules of the ethics review committee.

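### Patients already on chemotherapy and patients about to start are pooled in one arm contrast, which is unbiased for the enrolled mix but cannot separate prevention from alleviation and forgoes some precision

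*Protocol article*

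**What the plan says.** All references are to the protocol article.

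- **Population.** The third criterion under Inclusion and Exclusion Criteria admits patients who "are currently undergoing or just about to commence a comprehensive treatment of chemotherapy". Study Design and Results describe the same mixture.
- **Exclusion.** The first exclusion in the same section is having "undergone chemotherapy within the last 2 years".
- **Condition at entry.** The Abstract (Methods) states: "We will enroll 168 older patients with cancer with clinically confirmed chemobrain".
- **Aim.** The Abstract (Conclusions) states: "This efficacy trial will explore whether Chinese electroacupuncture can prevent chemobrain, alleviate the related symptoms". The Assessments section describes the primary outcome as being to "verify whether EA is therapeutically useful for preventing chemobrain and alleviating the related symptoms".
- **Clock.** The Abstract (Results) states: "These outcomes will be measured at 2, 4, 6, and 8 weeks after the randomization". Nothing links baseline to the first cycle or to a cycle number.
- **Allocation.** Randomization and Allocation Concealment specifies 1:1 allocation by "computer-generated block randomization with random block sizes", in sealed envelopes, and names no stratification factor.
- **Analysis.** Statistical Analyses compares accumulated incidence over 8 weeks by a Kaplan-Meier method and fits a mixed model with time and group as fixed factors. It says that participants' "age, chemotherapeutic drug dosage, fatigue at baseline, depression, and additional treatments will be considered as covariates". Chemotherapy status, cycle number and time since first dose are not listed.

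**The concern.** The two kinds of patient start from different places. Before the first cycle, baseline precedes exposure to the current course, so a later fall in cognition is something EA might prevent. Mid-course, baseline is already measured on cytotoxic drugs, so an improvement is something EA might relieve. A single arm difference averages over both, and the stated conclusion claims both.

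The incidence analysis sharpens the problem. A patient who is already impaired at baseline is not at risk of becoming impaired, and the article does not say how such patients enter the comparison. The impairment threshold also appears to be set from the baseline scores of all participants, so it would depend on the mix.

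At stake is mainly interpretation: a positive result could be reported as prevention when it came only from relief, or the reverse. A smaller cost is precision, because a factor that the protocol's own account makes prognostic is left out of both the allocation and the model.

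**Working it through.** **Inputs from the article:** 84 per arm, 20% dropout (84 × 0.8 ≈ 67 evaluable), control incidence 30%, sought reduction 10 to 20 points (read as percentage points). The 84 is taken as given. It does not follow from the stated inputs: with the printed formula's denominator squared, 30% v 10% and the stated multiplier, 10.5 × 0.30/0.04 = 78.75, so 79 per arm, or 99 after dropout. That is a separate matter and does not decide this point.

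**Assumptions, because the article gives neither:** the share of patients not yet started (50% unless stated), and an 8-week incidence gap between the two status groups of 10, 20 or 30 points.

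**1. Chance imbalance in status between arms**

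SD of the difference in shares = √(2 × 0.5 × 0.5/n).

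| n per arm | SD | 95% limit (1.96 × SD) |
|---|---|---|
| 84 | 7.7 points | 15.1 points |
| 67 | 8.6 points | 16.9 points |

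At the 84-per-arm limit, the shift in the arm difference is 0.151 × (10, 20, 30) = 1.5, 3.0, 4.5 points. At one SD it is 0.077 × (10, 20, 30) = 0.8, 1.5, 2.3 points. By exact binomial calculation, the chance of an imbalance of at least 10 points is about 19% with a 50/50 mix and 13% with a 25/75 mix. These figures treat allocation as simple, so they are an upper guide.

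**2. Comparison with the sampling error**

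For 30% v 10% with 67 per arm, SE = √((0.21 + 0.09)/67) = 6.7 points, and the 95% half-width is 13 points. The shifts in step 1 are part of this error, not an addition to it.

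**3. Precision left on the table**

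With a 50/50 mix and 30% overall incidence, the share of outcome variance explained by status is (d²/4)/0.21:

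- d = 10 points: 0.0025/0.21 ≈ 1%
- d = 20 points: 0.0100/0.21 ≈ 5%
- d = 30 points: 0.0225/0.21 ≈ 11%

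The SE would shrink by a factor of about √(1 − share), that is by about 1% to 6%.

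**4. Dilution if EA works in only one status group**

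Pooled difference = share × 20 points. Control risk is 30%, with 67 per arm and a two-sided 5% test of two proportions.

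| Share of patients in the responsive group | Pooled difference | Power |
|---|---|---|
| 100% | 20 points | 83% |
| 75% | 15 points | 55% |
| 50% | 10 points | 27% |
| 25% | 5 points | 9% |

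**5. Precision within a status group**

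Testing 30% v 10% within one group has about 53% power with 33 per arm (half of 67) and 29% with 16 per arm (a quarter of 67).

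**6. Do both groups exist?**

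Read literally, the first exclusion removes anyone now receiving chemotherapy, whom the third inclusion criterion admits. The Abstract's requirement of confirmed chemobrain leaves no unimpaired patient in whom it could be prevented. Yet the aim includes prevention, and the trial is sized and analysed on incidence. The size of either group cannot be known until these statements are reconciled.

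**The case against.** **Bias between arms.** A reader might infer that prevention and treatment effects are confounded, so that the arm comparison is biased. The documents do not support that. Status is fixed before a concealed 1:1 allocation and is balanced in expectation. The pooled contrast is valid as an average over whoever is enrolled, and chance imbalance is already within its standard error. This objection stands in full.

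**Existing adjustment.** A reader might also infer that nothing in the plan mitigates an imbalance. The mixed model uses the baseline assessment and random intercepts, so stable differences in starting level are partly absorbed. Drug dosage and additional treatments are listed as covariates. This stands in part: differences in course over the 8 weeks are not absorbed, and dosage, which the article leaves undefined, does not clearly encode whether or when chemotherapy began.

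**Status is not the same as the question asked.** It is tempting to equate not-yet-started with prevention and under way with alleviation. The Abstract says that every participant enters with confirmed chemobrain, so that split is not the protocol's own. This stands. The claims must depend on impairment at baseline as well as on chemotherapy status.

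**A condensed article and a pragmatic population.** Stratification factors may appear in a full protocol that is not shown, and enrolling both kinds of patient is a legitimate choice. Silence on stratification is therefore not itself the fault. The fault is that the stated population, clock, double claim, model factors and covariate list do not fit together.

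**Conclusion.** The point holds as one of interpretability and modest efficiency, not of validity. The pooled arm difference estimates an average effect over an unspecified mix and cannot support separate claims of prevention and alleviation.

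The precision forgone is small: about 1% to 11% of outcome variance for assumed incidence gaps of 10 to 30 points and an assumed 50/50 mix. The article gives no figure from which to judge the gain for MoCA. The dilution figures (83% power falling to 27% if only half the patients can respond) are conditional on an effect confined to one status group, which the documents neither state nor exclude. Adjustment would not recover that loss.

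The change is worth making because the factor is known at entry and costs almost nothing to use. It depends on first resolving the contradictions over who is eligible and whether participants are already impaired.

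**What to change.** 1. **Reconcile first.** The sponsor should settle the third inclusion criterion against the first exclusion, and the requirement of confirmed chemobrain against the prevention aim. If only one group remains, the rest of this fix shrinks accordingly.
2. **Model.** Add chemotherapy status at randomisation (not yet started versus under way) as a fixed factor in the mixed model, and stratify the log-rank comparison that accompanies the Kaplan-Meier curves by it.
3. **Report.** Give the arm difference by status as descriptive estimates with confidence intervals, stating that precision is low.
4. **Allocation.** Stratify the remaining envelopes by status where feasible. The article reports 11 of 168 recruited by 21 October 2023. If recruitment is now far advanced, steps 2, 3 and 5 still apply.
5. **Claims.** Do not claim prevention from the pooled result. Limit 'prevent' to participants who were unimpaired at baseline and had not yet started, and 'alleviate' to those impaired at baseline.

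**Cost:** a second set of envelopes and one variable already known at entry. Patients already randomised are adjusted for but not stratified. The within-group estimates are imprecise (about 53% power for 30% v 10% at 33 per arm, 29% at 16), so they should not carry confirmatory claims.
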